### 8.4.3 Reporting Unanticipated Problems to Participants

All serious, unexpected, and related adverse events that are unresolved at the time of the patient's termination from the study or discharge from the hospital will be followed by the research staff until the events are resolved, the patient is lost to follow-up, the adverse event is otherwise explained or has stabilized. If the local IRB determines an unanticipated problem to pose harm to the participating patients, the site investigator will contact the patient with a letter and a phone call. This letter will describe the unanticipated problem and if any follow-up or additional care is needed.

# 9 Statistical Considerations

## 9.1 Statistical Hypotheses

The pilot study is not designed to test an efficacy hypothesis, but rather to determine the feasibility for patient enrollment and the number of doses received per patient.

**Our primary hypothesis** for the single site and the multi-site study is that we can enroll at least 0.6 patients per site per month and deliver a minimum of two out of three planned nebulized TXA doses to >90% of enrolled patients.  The single site study will only be one year and the multi-site study for 18 months. We will test each of this (yes/no) hypothesis using a Mantel Haenszel test stratified by site for a total of 12 patients for the single-site study for greater than 24 nebulization and for the multi-site study up to 22 patients with greater than 44 nebulization's recorded as delivered.

**Our secondary goals** will be to determine if nebulized TXA prevents going to the OR for PTH and utilization of blood products. These goals are not powered to be tested in the pilot study. **Our second aim** is to verify a pulmonary physiological based pharmacokinetic (PBPK) model (i.e., nasal cavity, pharynx, and lungs) will predict the change in the area under the curve (AUC0-α) of TXA concentration in systemic compartments with accuracy (average absolute fold error <2) and precision (average fold error <2). We will calculate the AUC of accuracy and precision of the model using the linear trapezoid rule. For the PBPK model, we will use previously published PK data to construct the model before verifying it with systematic samples.

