| **Description of Sites/Facilities Enrolling Participants:** | The University of Texas Health Science Center/University Health System for single site study then will expand to University of California at Davis, and Hasbro Children Hospital/Brown University School of Medicine | |  |  |
| **Description of Study Intervention:** | After randomization, children will receive three TXA nebulization doses (500 mg each) or three saline nebulized doses (placebo). | |  |  |
| **Study Duration:** | Study 1: 12 months, Study 2: 12 to 18 months | |  |  |
| **Participant Duration:** | Thirty days after randomization | |  |  |

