# 3 Objectives and Endpoints

| OBJECTIVES | ENDPOINTS | JUSTIFICATION FOR ENDPOINTS |
| --- | --- | --- |
| Primary | | |
| Evaluate the feasibility to enroll 0.6 patients/site/month  Nebulize at least two of three doses of TXA to children with PTH.  Determine the local and systematic concentrations of nebulized TXA in children  Determine incidence of adverse and serious adverse events | Enrollment after one year and % of nebulization’s. Go/no-go threshold is 0.6 patients per site per month for a total of 22 patients. Time and success to obtain consent will establish need for exception for informed consent (EFIC).    The goal is >90% of patients will receive at least two of three planned nebulization of TXA.  Collection of two blood samples from each participant. This will verify a pulmonary physiological-based PK model (PBPK) (i.e., nasal cavity, pharynx, and lung) that indirectly predicts the oropharyngeal and systematic concentration of nebulized TXA.  A phone call or email will be placed to participants at 30 +/- 5 days. | The overall incidence of PTH is 5%, yet numbers per site may be very different. Assessment and consent will optimize site selection, recruitment process, and the plan the main trial.    The establishment of a pragmatic protocol design will help design a large trial.  Limited data on nebulized TXA systematic absorption. Topical PK studies of TXA document a significant reduction in systematic levels but the same hemostasis effect.  Safety Evaluation as recommended by the FDA. |
| Secondary | | |
| Determine the number and rationale for PTH patients to return to the OR; and    Determine the number of blood transfusions and estimated blood loss and      Determine the recurrence of PTH after TXA, saline, or return to the OR. | Collection number participants and surveys on ENT surgeons’ decision to go to the OR    Collection of electronic health record data on number of blood transfusions and estimated blood loss    Survey families to determine PTH recurred seven days from randomization. | To evaluate if return to the OR can be an outcome for the main trial.    To evaluate if TXA decreased severity of PTH bleeding.      To evaluate if TXA or return to OR prevented PTH recurrence. |
| Tertiary/Exploratory | | |

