# 4 Study Design

## 4.1 Overall Design

Our overall hypothesis for the phase 3 trial is that nebulized TXA will decrease the severity of bleeding and the need for repeat surgical intervention for PTH. To test this hypothesis, we first propose to conduct a multi-center, randomized controlled, blinded pilot trial (phase 2) to assess the feasibility, safety, and the local and systematic absorption of nebulized TXA in children with PTH. Safety and pharmacokinetic data are well known for topical and intravenous administration of TXA but there is limited data on nebulized delivery of TXA. Participants will be randomized at the time of the consent in the emergency department. Earlier PECARN studies experience suggest that pre-consenting patients in surgical clinic will not improve participant enrollment or completion. Children 2 to 17 years old presenting to the ED with PTH will be randomized in a 1:1 ratio to three doses TXA or placebo (saline).  All interventions will be blinded by the investigator, treating clinical care team, and research staff. Only the pharmacist and biostatistician will know the randomization schedule. We will not unblind patients as there is no reversal agent. Clinical teams will be asked to assume the patient received TXA. Patients will be followed during their hospital course and outcomes will be evaluated at seven +/- 1 days after randomization. As this is a pilot study, no stratification or interim analysis will be performed.

[figure not shown]

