## 5.5 Strategies for Recruitment and Retention

The pilot study aims to test the feasibility of enrolling 0.6 patients per site per month. The specific goal for this pilot trial is to enroll 12 patients (6 treatment groups & 6 control group) at the University of Texas Health Science Center (UTHSCSA)/University Hospital in San Antonio, TX. The participants will be children who present to the emergency department (ED) with secondary posttonsillectomy hemorrhage (PTH) occurring 24 hours or more after their tonsillectomy. PTH patients will be screened and approached in the ED. Participants will be followed as outpatients for one week post-randomization. Due to the short follow-up period, we do not expect a significant loss of participants. However, text, phone, and e-mail information will be obtained from each participant to give the study team multiple options for gathering data on secondary and tertiary objectives. In this pilot analysis, we will offer participants an incentive to complete all study procedures. We will also closely monitor study completion to determine if participant incentives are necessary for the main trial. This pilot study will help assess the feasibility of enrollment rates and the effectiveness of follow up methods, which will inform the design and implementation of the larger main trial.

The investigators will enroll at the University of Texas Health Science Center (UTHSCSA)/University Hospital in San Antonio, TX for the single site and the multi-site study, the University of California at Davis Medical Center in Davis, CA, and Hasbro Children’s Hospital in Providence, RI. Each of the ENT and ED colleagues at each site have provided the incidence of PTH, percentage that return to the OR, and the monthly ED visit rate. Previous studies document that PTH primarily presents at night, therefore we arrange for 24/7 coverage at each site.

| **Site** | **Annual PTH Incidence** | **Going to OR** | **Monthly ED Visits** |
| --- | --- | --- | --- |
| San Antonio, TX | 5.4% | 73% | 1.60 |
| Davis, CA | 3.2% | 70% | 0.63 |
| Providence, RI | 2.8% | 63% | 2.80 |

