# 8 Study Assessments and Procedures

## 8.1 Efficacy Assessments

The **primary feasibility outcomes** for the pilot trial are the enrollment rate (patients per site per month) and the proportion of patients receiving study drugs (at least 2 nebulized doses).  Safety is always an outcome, and all adverse events will be reviewed.

**The secondary outcome is** the ENT surgeon rationale, decision (Y/N) for the PTH patient to return to the OR, severity of bleeding with estimates of blood loss that include volume of hemorrhage recorded blood loss, and the number of blood transfusions. Additionally, we will determine the indirect local and systematic concentration of nebulized TXA by verifying our pulmonary physiologically based pharmacokinetic model. To verify the model, two lab samples will collect at opportunistic times either by finger stick or ad**. The study is not** powered for the secondary outcomes as this a pilot trial.

The **exploratory outcomes** will be age-appropriate pain scores and parent and child anxiety scales as measured by anxiety-state-trait scale (STAI). For children under eight years old their anxiety will be measured by STAI-C, which utilized pictures These will be exploratory as the pilot trial is not powered to determine the change in the outcomes.  Please see **Figure 7** for a timeline of all study procedures and outcomes.

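### The primary delivery criterion counts TXA doses over all enrolled patients, half of whom get saline, so it is capped at 50% and cannot exceed 90%

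*Protocol*

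**What the plan says.** Section 9.1 states the delivery half of the primary hypothesis as "deliver a minimum of two out of three planned nebulized TXA doses to >90% of enrolled patients". The endpoint table in section 3 repeats it: "The goal is >90% of patients will receive at least two of three planned nebulization of TXA". The second primary objective in the synopsis (1.1) and the text under the schema (1.2) also name TXA.

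Patients "will be randomized in a 1:1 ratio to three doses TXA or placebo (saline"), and the single-site target is to "enroll 12 patients (6 treatment groups & 6 control group"). The synopsis says that "children will receive three TXA nebulization doses (500 mg each) or three saline nebulized doses (placebo").

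Section 8.1 words the same feasibility outcome differently, as "the proportion of patients receiving study drugs (at least 2 nebulized doses"). Section 9.1 also attaches a total dose count to the hypothesis at the first stage: "for a total of 12 patients for the single-site study for greater than 24 nebulization". The later stage, with three centers, has a count of its own, set as "up to 22 patients with greater than 44".

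**The concern.** The numerator is patients who received at least two TXA doses, and the denominator is everyone enrolled. A child assigned to saline is in the denominator and can never enter the numerator. The criterion therefore measures the allocation ratio as much as delivery.

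Section 9.1 treats this as a yes/no hypothesis. Read literally, the answer is no whatever happens at the bedside. Whoever scores it must choose a repair, and the two obvious ones (count study drug in both arms, or restrict to the TXA arm) have different denominators and pass marks. If the choice is made after the data are seen, the feasibility verdict loses force. The dose counts in the same paragraph add a further rule that does not agree with the patient-level one.

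**Working it through.** **Inputs.** Single site: 12 patients, 6 per arm (5.5). Multi-site: up to 22 patients (9.1); 11 per arm is assumed from the 1:1 ratio (4.1). Planned doses: three per patient in either arm (1.1). Threshold: above 90% of patients with at least two doses (9.1, section 3).

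**1. The protocol's own counts.** Two doses × all enrolled: 2 × 12 = 24 and 2 × 22 = 44. Both match section 9.1. Two doses × TXA arm only: 2 × 6 = 12 and 2 × 11 = 22. Neither matches. If only TXA doses counted, the largest possible totals would be 3 × 6 = 18 and 3 × 11 = 33, below 24 and 44. The counts were therefore built on both arms.

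**2. Literal criterion under perfect delivery.** Maximum share = TXA patients / all enrolled = 6/12 = 11/22 = 50%, so more than 90% is unattainable.

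**3. Pass marks under the two repairs** (smallest k with k/n above 0.90).

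| Study | Both arms pooled | TXA arm only |
|---|---|---|
| Single site | 11/12 = 91.7% | 6/6 = 100% (5/6 = 83.3% fails) |
| Multi-site | 20/22 = 90.9% | 10/11 = 90.9% |

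At the single site, one miss in a TXA child gives 11/12 (pass) pooled and 5/6 (fail) in the TXA arm. Two misses, both in saline children, give 10/12 = 83.3% (fail) pooled and 6/6 (pass) in the TXA arm.

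**4. Chance of passing.** Exact binomial upper tail. The protocol gives no expected delivery rate, so the true rate is an assumption, taken as the same in both arms and independent between patients.

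| Assumed true rate | Single site, pooled (n=12) | Single site, TXA arm (n=6) | Multi-site, pooled (n=22) | Multi-site, TXA arm (n=11) |
|---|---|---|---|---|
| 0.95 | 0.882 | 0.735 | 0.905 | 0.898 |
| 0.90 | 0.659 | 0.531 | 0.620 | 0.697 |
| 0.85 | 0.443 | 0.377 | 0.338 | 0.492 |
| 0.80 | 0.275 | 0.262 | 0.154 | 0.322 |

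**5. Dose counts against the patient rule, both arms counted.**
- Every patient receives exactly two doses: 100% meet the patient rule, but the totals are 24 and 44, which do not exceed 24 and 44. Patient rule passes, count fails.
- Single site, 7 patients with three doses and 5 with one: 7 × 3 + 5 × 1 = 26, above 24. Count passes, yet only 7/12 = 58% meet the patient rule.
- Multi-site, 12 patients with three and 10 with one: 12 × 3 + 10 × 1 = 46, above 44. Count passes at 12/22 = 55%.

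**The case against.** The strongest reply is that the intent is plain. Section 8.1 says study drug, section 9.1 opens by speaking of doses received per patient, the synopsis endpoint names no drug, and 24 and 44 can only come from both arms. On this view TXA is loose shorthand for study drug. That stands as evidence of intent, and it means this is a wording and denominator error. It does not correct the rule: four places name TXA, none defines the above-90% criterion over both arms, and section 9.3 lists patients who received TXA as a separate population, which leaves a TXA-only reading open. Nor is this a detail left to an analysis plan, since the protocol itself states the numerator and denominator.

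It can also be said that little depends on the result. The go/no-go threshold in sections 3 and 9.2 concerns enrollment only, and section 9.4.1 calls for descriptive analysis of feasibility outcomes. That limits the consequence, but section 9.1 still sets delivery as a primary yes/no hypothesis.

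A reader might infer two stronger things. One is that scoring the TXA arm alone would break the blind. The documents do not support this: sections 4.1 and 6.3 already give the randomization schedule to the biostatistician, who could compute an arm-specific proportion without unblinding investigators, clinicians or research staff. The other is that the choice of repair matters equally in both studies. It does not: at 95% delivery the multi-site chances of passing are 0.905 and 0.898, and at 90% the order reverses.

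**Conclusion.** The delivery criterion cannot be met as written: its ceiling is 50% against a threshold above 90%. The single-site ceiling rests on the stated 6 and 6; the multi-site one assumes 11 and 11. This is a defect in the stated rule and does not show that delivery or the design is infeasible.

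The likely intent is study nebulizations in both arms. Until the protocol says so, the single-site verdict can depend on the reading: 11 of 12 against 6 of 6, with chances of passing of 0.88 and 0.74 at an assumed 95% rate. In the multi-site study the readings are nearly equivalent at that rate; at lower assumed rates the TXA-arm rule is the easier one to pass. Separately, the dose counts conflict with the patient-level rule in both directions, even when both arms are counted. The criterion should be corrected before it is scored.

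**What to change.** - In the synopsis objective (1.1), the schema text (1.2), the section 3 endpoint table and section 9.1, replace TXA in this criterion with assigned study drug (TXA or saline).
- Define the endpoint once: the proportion of patients, both arms pooled, who receive at least two of the three planned study nebulizations. Pass means above 90%. Give counts only as examples (11 of 12, 20 of 22) and recalculate for the actual number, since section 9.1 allows up to 22 and the synopsis up to 30.
- State whether patients who are randomized but untreated, and replaced under section 7.2, stay in the denominator.
- Remove the counts of more than 24 and more than 44 nebulizations as a pass rule, or label them descriptive.
- Report delivery by arm descriptively.

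The cost is a wording amendment in four places plus one sentence on replacements. It needs no new data and no change to treatment or sample size.

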# 1 Protocol Summary

## 1.1 Synopsis

| **Title:** | TranExamic Atomized for Pediatric post-Operative Tonsillectomy hemorrhage: A Pilot and Feasiblity Study |  |  |  |
| --- | --- | --- | --- | --- |
| **Study Description:** | This study starts as single site pilot study, randomized, double-blinded controlled trial for 12 patients. Then dependent on funding, the study will be a multi-center, randomized, double-blinded, placebo-controlled trial. It is a parallel arms pilot trial randomizing up to 30 patients. |  |  |  |
| **Objectives:** | \| Primary Objective: \| The primary objectives of this pilot study are:   1. Enroll 0.6 patient's/site/month with PTH and 2. Evaluate the ability to nebulize at least two doses of TXA to children with PTH and 3. Determine the indirect local and systematic concentrations of nebulized TXA in children 4. Adverse events will be assessed 30 +/- 5 days from randomization \| \| \| \| --- \| --- \| --- \| --- \| \| Secondary Objectives: \| The secondary objectives of this pilot study are:   1. Determine the number and rationale for PTH patients to return to the OR; and 2. Determine the number of blood transfusions and estimated blood loss and 3. Determine the recurrence of PTH after TXA, saline or return to the OR. \| \| \| \| Exploratory Objectives: \| \| Establish pain and anxiety inventory at 7 +/- 1 from randomization. \| | | |  |
| **Endpoints:** | \| Primary Endpoint: \| Enrollment after one year, % of nebulization administered to patient's enrolled, and collection of two blood samples from each participant. Adverse events will be assessed at 30 +/- 5 days from randomization. \| \| --- \| --- \| \| Secondary Endpoints: \| Collection of surveys on ENT decision to go to the OR, electronic health record data on blood transfusions and estimated blood loss, and if PTH recurrences within seven days of randomization. \| \| Exploratory Endpoints: \| Age-appropriate pain and anxiety states at 7 +/- 1 days after randomization. \| | | | |
| **Study Population:** | Children aged 2 to 17 years old that present with post-tonsillectomy hemorrhage (PTH), ENT clinicians, parents of the children enrolled and missed eligible. | |  |  |
| **Phase:** | 2 | |  |  |

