## 9.2 Sample Size Determination

Multiple studies suggest that 76% of children with PTH go to the OR for surgical control of their hemorrhage. This pilot study sample size is based on the goals for the subsequent phase 3 trial. Conservatively, we estimate that nebulized TXA will decrease the incidence of surgical care for PTH from 76% to 61%, or in other words a 15% effect size.  The sample size for phase 3 trial based on an effect size of 0.15 with randomization of 324 children with PTH using an a priori, one-tailed, Fishers exact test stratified by site, with 80% power, alpha=0.025. This trial will then need to enroll at least 0.6 patients per site per month at 12 sites over 4 years (0.563 patients x 12 sites x 48 months = 345 patients). Thus, the go/no-go threshold for the subsequent phase 3 trial is an enrollment goal of 0.6 patients per site per month in this pilot study. For the single site trial designed for one year, we hope to enroll 12 patients. For the mutli-site study we hope to enroll 22 patients’ across 3 enrolling sites over 12 months at 0.6 patients x 3 sites x 12 months = 21.6, rounded up to 22 targeted enrollments.

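### The multi-site go/no-go count of 22 matches the 0.6 rate only over 12 months, but Section 9.1 pairs 22 with 18 months, where it is 0.41 per site per month

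*Protocol*

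**What the plan says.** The objectives table in Protocol Section 3 gives the rule in both forms: "Go/no-go threshold is 0.6 patients per site per month for a total of 22 patients". The same table, and the primary endpoint in the synopsis (Section 1.1), assess enrolment at one year.

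Section 9.2 shows where the count comes from: "0.6 patients x 3 sites x 12 months = 21.6, rounded up to 22 targeted enrollments". It also names the rate, with no count, as the go/no-go threshold for the phase 3 trial.

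Section 9.1 states the primary hypothesis for both stages, that "we can enroll at least 0.6 patients per site per month". It then gives the durations, "The single site study will only be one year and the multi-site study for 18 months", and attaches a number to each yes/no test: 12 for the single site and, "for the multi-site study up to 22 patients".

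The synopsis gives the study duration as "Study 1: 12 months, Study 2: 12 to 18 months" and the size as "It is a parallel arms pilot trial randomizing up to 30 patients". Sections 5.5 and 9.2 describe the 12 single-site patients as a goal or hope for one year of enrolment.

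**The concern.** Enrolment is a primary endpoint and decides whether phase 3 proceeds. A rate and a count are interchangeable only when the site-months are fixed. Here the count was worked out for 12 months, while the section stating the hypothesis gives the study 18. A multi-site stage that reaches its 22nd child in month 18 meets the count in Section 3 and misses the rate in the same sentence by about a third.

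The threshold exists to secure phase 3 accrual, which Section 9.2 puts at 324 children from 12 sites in 48 months. At 22/54 per site per month, 12 x 48 = 576 site-months would yield about 235 children. A go based on the count at month 18 could therefore endorse a trial that would not fill on its own plan.

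**Working it through.** **Inputs.** Rate 0.6 per site per month (Sections 1.1, 3, 9.1, 9.2); 3 sites (9.2); multi-site duration 12 months (9.2), 18 months (9.1) or 12 to 18 months (1.1); count 22 (3, 9.1, 9.2); ceiling 30 (1.1); single site 12 patients in 12 months (9.1, 9.2).

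**Formulas.** Count = rate x sites x months; rate = count / (sites x months).

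**The plan's own figure.** 0.6 x 3 x 12 = 21.6, rounded up to 22. It reproduces. In reverse, 22 / 36 = 0.61, which meets 0.6.

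**With 18 months.**
- Children needed: 0.6 x 3 x 18 = 32.4, so 33.
- Rate implied by 22: 22 / 54 = 0.41.
- Latest time at which 22 still meets 0.6: 22 / (0.6 x 3) = 12.2 months.

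**Chance that the count is reached when the rate is too low.** Assume Poisson accrual, three sites open throughout and a true rate of 0.50, which is below threshold.
- 12 months: mean 0.50 x 36 = 18; P(at least 22) = 0.20.
- 18 months: mean 0.50 x 54 = 27; P(at least 22) = 0.86.

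**Ceiling of 30.**
- Over 18 months, 30 / 54 = 0.56. Over 12 months, 30 / 36 = 0.83.
- Thirty children meet 0.6 if enrolled within 30 / 1.8 = 16.7 months.
- The 33 needed over 18 months exceeds 30.
- If 30 covers both stages, 12 + 22 = 34 also exceeds it.

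**Single site.** 0.6 x 1 x 12 = 7.2, so 8 children meet the threshold. Twelve children is 12 / 12 = 1.0 per month. At a true rate of exactly 0.6 (mean 7.2), P(at least 12) = 0.06 and P(at least 8) = 0.43.

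**The case against.** The strongest reply is that the time point is already fixed. The synopsis endpoint, the objectives table and Section 9.2 all point to one year, where 22 and 0.6 agree. Section 9.2 already makes the rate the threshold. The synopsis line is labelled study duration, and the 18 months in Section 9.1 may include start-up and follow-up. Section 9.4.1 adds that feasibility outcomes are analysed descriptively.

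Much of this stands. It shows that the multiplication in Section 9.2 is right and that 12 months is the better-supported reading. It also means that the 86% applies only if accrual is counted to 18 months. It does not remove the conflict. Section 9.1 ties 18 months and 22 patients to the same yes/no hypothesis, and nowhere does the protocol say that the extra six months is something other than accrual. Participant follow-up is only thirty days, so follow-up alone would not explain the gap.

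A reader might infer three stronger points that the documents do not support:
- **That the single-site target contradicts the threshold.** Twelve is a hoped-for number above a floor of at least 0.6, and a target may exceed a floor. The residue is that Section 9.1 attaches 12 to the test, so it is unclear whether 8 to 11 children would pass.
- **That the ceiling of 30 makes 0.6 unattainable.** It is only a maximum, and 30 enrolled within 16.7 months meets the rate. Whether it includes the single-site children is not stated.
- **That every site must reach 0.6, which would be very demanding for the site with 0.63 visits a month (Section 5.5).** Section 9.2 multiplies across three sites to one total, and Section 3 gives a total and expects site numbers to differ. Both point to a pooled rate.

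**Conclusion.** The concern holds for the multi-site stage. Rate 0.6, count 22 and an 18-month accrual window cannot all be true: 18 months needs 33 children, and 22 gives 0.41. With a true rate of 0.50, the choice of window moves the chance of reaching the count from about 20% to about 86%. Those probabilities assume Poisson accrual and all three sites open for the whole window; the 0.50 is illustrative.

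The single-site 12 and the ceiling of 30 are matters for clarification and not further contradictions. Because the one-year endpoint and the derivation of 22 agree with each other, this is a point that should be fixed and does not by itself invalidate the design.

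**What to change.** In Sections 1.1, 3 and 9.1:

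- Make the sole go/no-go criterion the pooled rate, children enrolled divided by actual site-months open to enrolment, at least 0.6, assessed at 12 months of enrolment. Give 22 as the count derived from it for three sites open throughout.
- Say what 18 months means. If it is total study duration including start-up and follow-up, state that. If it is the accrual window, the matching count is 33, and the ceiling of 30 must be reconciled with it.
- For the single site, state that 0.6 corresponds to 7.2 children in 12 months, so 8, and that 12 is a target and not the pass mark.
- State whether the ceiling of 30 includes the 12 single-site children. No particular new ceiling follows from the documents, and Section 7.2 allows replacements, so some headroom may be intended.

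The cost is wording only, with no added patients or procedures. The downside for the sponsor is that slow accrual can no longer be read as success by running longer.

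### The Mantel-Haenszel test named for the two primary feasibility hypotheses does not address them, and the >24/>44 nebulization totals can contradict the per-child delivery endpoint

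*Protocol*

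**What the plan says.** Section 9.1 states the primary hypothesis in two parts, for both the single-site and the multi-site study: that "we can enroll at least 0.6 patients per site per month", and that the team can "deliver a minimum of two out of three planned nebulized TXA doses to >90% of enrolled patients".

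It then names the analysis: "We will test each of this (yes/no) hypothesis using a Mantel Haenszel test stratified by site for a total of 12 patients". The same sentence continues "for the single-site study for greater than 24 nebulization". Its counterpart for the larger stage reads "for the multi-site study up to 22 patients with greater than 44 nebulization's recorded as delivered".

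Elsewhere delivery is defined per patient. Section 3 says "The goal is >90% of patients will receive at least two of three planned nebulization of TXA". Section 8.1 gives the outcome as "the proportion of patients receiving study drugs (at least 2 nebulized doses". The Synopsis (Section 1.1) instead words the endpoint as a percentage of nebulizations given.

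Section 9.4.1 says that feasibility outcomes will be analysed descriptively. Section 9.4.2 uses the same site-stratified Mantel-Haenszel test to compare TXA with saline on surgical intervention, which is a genuine two-group question.

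**The concern.** A Mantel-Haenszel test assesses association between two categorical variables across strata. Neither feasibility hypothesis is an association: one compares a rate with 0.6, the other a proportion with 90%. The single-site stage also has only one stratum. So the named test would not answer either question, and Section 9.4.1 points to a different, descriptive analysis.

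The totals raise a second problem. A sum of doses over all children is not the share of children who received at least two, because a third dose in one child can offset a missing dose in another.

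Feasibility is the declared purpose of this pilot. If the total is used as the criterion, a primary outcome could be reported as missed when every child met it, or as met when little more than half did. Choosing between the two definitions after the data are seen would be post hoc.

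**Working it through.** **Inputs.** Three planned doses per child (Synopsis). Single-site stage: 12 children, 6 per arm (Section 5.5). Multi-site stage: up to 22 (Section 9.1). Delivery goal above 90% with at least two doses (Sections 3 and 9.1). Cut-offs above 24 and above 44 (Section 9.1).

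**1. Reproducing the cut-offs.** 12 × 2 = 24 and 22 × 2 = 44. They are the number of children times two doses.

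**2. What the per-child criterion requires.** The smallest count above 90%:
- n = 12: 10/12 = 83.3%, 11/12 = 91.7%, so at least 11.
- n = 22: 19/22 = 86.4%, 20/22 = 90.9%, so at least 20.

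**3. Where the total fails although the endpoint is met.** If every child receives exactly two doses, 100% meet the endpoint. The totals are 24 and 44, and neither exceeds its cut-off.

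**4. Where the total passes although the endpoint is missed.** Let k children receive three doses.
- The others receive one: total = 3k + (n − k) = n + 2k. For n = 12, 12 + 2k > 24 needs k = 7: total 26, 7/12 = 58.3%. For n = 22, 22 + 2k > 44 needs k = 12: total 46, 12/22 = 54.5%.
- The others receive none: total = 3k. For n = 12, k = 9: total 27, 75%. For n = 22, k = 15: total 45, 68.2%.

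**5. How often the two disagree.** Over all ways of splitting the children into 0, 1, 2 or 3 doses:

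| n | Patterns | Total passes, endpoint missed | Total fails, endpoint met |
| --- | --- | --- | --- |
| 12 | 455 | 52 | 6 |
| 22 | 2300 | 294 | 18 |

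Pattern counts are not probabilities. As an illustration, assume that each child independently receives all three doses with probability p and otherwise none. The protocol gives no value for p, so a range is shown.

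| p | n = 12: total passes | n = 12: endpoint met | n = 22: total passes | n = 22: endpoint met |
| --- | --- | --- | --- | --- |
| 0.70 | 0.49 | 0.09 | 0.67 | 0.02 |
| 0.75 | 0.65 | 0.16 | 0.84 | 0.06 |
| 0.80 | 0.79 | 0.27 | 0.94 | 0.15 |

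**6. What a Mantel-Haenszel test of delivery would show.** Cross arm with delivery, 6 children per arm, one stratum. The numerator is the observed successes on TXA minus their expected number.
- 3/6 in each arm (50% delivery): 3 − 6 × 6/12 = 0. No difference is shown, although the goal is clearly missed.
- 6/6 in each arm (100% delivery): 6 − 6 × 12/12 = 0, and the variance is also 0 because there are no failures, so the statistic is undefined.

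For enrolment there is no such table: the quantity is a count over site-months.

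**7. Would a one-sample test serve instead?** No alpha is stated for the feasibility hypotheses. Taking 90% as a null value at an assumed one-sided 5% level, the best possible results give p = 0.9^12 = 0.28 for 12/12 and 0.9^22 = 0.098 for 22/22. Rejection would need at least 29 of 29. At these sizes the workable form is a count criterion with an interval.

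**8. Intervals to report (exact 95%).**
- Delivery: 11/12, 61.5% to 99.8%; 20/22, 70.8% to 98.9%.
- Enrolment: 12 in 12 site-months is 1.00 (0.52 to 1.75); 22 in 36 site-months is 0.61 (0.38 to 0.93).

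**The case against.** The best defence is that the protocol already defines delivery correctly, per patient, in Sections 3 and 8.1 and in the first half of the Section 9.1 paragraph. The sentence with the totals is garbled and never says that the hypothesis passes or fails on them. They may be only the expected number of doses at two per child. Section 9.4.1 already calls for description. This stands in part: the totals cannot be called a settled decision rule. But they sit inside the sentence that specifies the test, nothing labels them as expected volumes, and the Synopsis endpoint is also worded at dose level.

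Several stronger readings are tempting and are not supported.
- A reader might infer that delivery is a go/no-go gate for phase 3. Sections 3 and 9.2 attach that threshold to enrolment only; delivery is a goal and a primary feasibility outcome.
- A reader might infer that the totals always mislead. They do not: if every child receives three doses, 36 and 66 exceed the cut-offs and agree with the endpoint.
- A reader might infer that the test cannot be computed at all. For delivery an arm-by-outcome table exists and one stratum is no bar, although the statistic answers another question.
- The reference to TXA doses in more than 90% of enrolled patients cannot be met literally under 1:1 allocation to saline. Section 8.1 refers to study drugs, so this is loose wording rather than a separate defect.

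**Conclusion.** The concern holds in two parts. First, Section 9.1 names a test that addresses neither primary feasibility hypothesis and conflicts with the descriptive approach in Section 9.4.1; this needs no assumption. Second, the totals are not equivalent to the per-child endpoint. If they are used as the criterion, they can reject at 100% delivery and accept at 58% (n = 12) or 55% (n = 22). That part depends on reading the totals as a criterion, which the sentence allows but does not make certain.

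The go/no-go threshold for phase 3 is unaffected by the totals, and the pilot claims no efficacy inference. Severity: should-fix.

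**What to change.** In Section 9.1, delete the Mantel-Haenszel test of the feasibility hypotheses and both totals, in line with Section 9.4.1, and state two descriptive criteria:

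- **Delivery:** the proportion of children, both arms together, who receive at least two of three study nebulizations (TXA or saline). Met if above 90% at the achieved sample size (at least 11/12 or 20/22). Because the Synopsis allows up to 30 patients, state the rule as a percentage; at 30 it would need 28, since 27/30 is exactly 90%. Report an exact 95% interval.
- **Enrolment:** children enrolled per site-month. Met if at least 0.6. Report an exact Poisson interval.

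Use the same per-child wording in the Synopsis and Section 3. Fix one denominator, all randomised children including any untreated or replaced, and reconcile it with Section 7.2 (untreated children may be replaced) and Section 9.3 (populations defined by receipt). The choice matters. In a hypothetical case where two untreated children are replaced and the 12 treated all receive two or more doses, the result is 12/12 among the treated but 12/14 = 86% among the randomised.

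The cost is wording only, with no change to sample size or data collection. The downside is that no p-value is claimed and the intervals are wide (11/12: 62% to 100%), which reflects what a pilot of this size can show.
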